## Abstract

**Background:**

Emotional blunting is a symptom that has always been present in depressed patients. Repetitive transcranial magnetic stimulation (rTMS) is a safe and effective supplementary therapy for treating depression. However, the effectiveness and brain imaging processes of functional magnetic resonance imaging-guided personalized rTMS (fMRI-rTMS) in the treatment of depression with emotional blunting have not been observed in randomized controlled trials.

**Methods:**

This study is a randomized, controlled, double-blind, and single-center clinical trial in which 80 eligible depressed patients with emotional blunting will be randomly assigned to two groups: a functional magnetic resonance imaging-guided personalized rTMS (fMRI-rTMS) group and a control group. Individuals in the fMRI-rTMS group (*n* = 40) will receive high-frequency rTMS (10 Hz, 120% MT). The main target of stimulation will be the area most relevant to the functional connectivity of the right medial prefrontal cortex (mPFC) and amygdala. The control group (*n* = 40) will receive sham stimulation, with a coil flipped to 90 degrees relative to the vertical scalp. All patients will receive 15 consecutive days of treatment, with each session lasting half an hour per day, followed by 8 weeks of follow-up. The primary outcome is the comparison of Oxford Depression Questionnaire (ODQ) scores between these two groups at different time points. The secondary outcomes include evaluating other clinical scales and assessing the differences in brain imaging changes between the two groups before and after treatment.

**Discussion:**

This trial aims to examine the effects of functional magnetic resonance imaging-guided personalized rTMS (fMRI-rTMS) intervention on depressed patients experiencing emotional blunting and to elucidate the potential mechanism behind it. The results will provide new evidence for using fMRI-rTMS in treating depression with emotional blunting in the future.

**Trial registration:**

ClinicalTrials.gov INCT05555940. Registered on 13 September 2022 at http://clinicaltrials.gov.

**Supplementary Information:**

The online version contains supplementary material available at 10.1186/s13063-024-07976-3.

## Background

Depression is characterized by feelings of sadness, lack of interest and pleasure, and decreased energy, which can seriously influence personal, work, and family relationships [1]. Antidepressants remain the preferred treatment option at present. However, mainstream antidepressants, including elective selective serotonin reuptake inhibitors (SSRIs), and serotonin-norepinephrine reuptake inhibitors (SNRIs) are often reported to cause side effects such as emotional blunting [2].

Emotional blunting manifests as a decrease in the experience of both positive and negative emotions, a lack of empathy, indifference to others, avoidance, and disregard for responsibility, which seriously affects the quality of life in depression [3]. According to Ma et al., approximately 40% to 60% of patients with depression who use SSRIs or SNRIs experience emotional blunting to varying degrees [4]. Another study also indicated that emotional blunting was not only a side effect of antidepressants but also a residual symptom of incomplete treatment for depression [5]. Furthermore, emotional blunting may decrease patient compliance and result in relapse or symptom worsening [3]. Therefore, it is necessary to research and develop methods beyond drug therapy.

An effective and noninvasive method of neuromodulation is repetitive transcranial magnetic stimulation (rTMS) [6]. Although rTMS primarily focuses on specific localized areas, it has the potential to induce modifications in brain connectivity and functional alterations in various cortical regions [7]. The modulation of distal regions is achieved by stimulating proximal regions, indicating the presence of underlying regulatory mechanisms within the brain network during this process.

A meta-analysis of major depressive disorder (MDD) found reduced coupling between the medial prefrontal cortex (mPFC) and the amygdala [8]. Both the increase and decrease in emotion activate the prefrontal cortex, and the downregulation of emotion is related to more right-lateralized activity [9]. Limbic structures, such as the amygdala, are less responsive to emotional stimuli, and subjects experience emotional blunting [10]. Using rTMS to stimulate the right mPFC, researchers found that high-frequency (20 Hz) rTMS enhanced the functional connection between the right amygdala and mPFC, while low-frequency (1 Hz) rTMS weakened the functional connection [11]. Right-sided high-frequency stimulation of the dorsolateral prefrontal cortex attenuates the processing of negatively valenced emotional stimuli in the right amygdala of healthy women [12].

In clinical practice, the transcranial magnetic stimulation site is typically set 5–6 cm in front of the motor cortex. However, this method is inaccurate [13]. According to increasing amounts of evidence, personalized interventions enhance the efficacy of transcranial magnetic stimulation therapy [14–16]. Therefore, we hypothesized that compared with the sham stimulation group, stimulating the most relevant functional connection between the right mPFC and amygdala with fMRI-rTMS could increase prefrontal cortex activity and decrease amygdala activity, thereby alleviating symptoms of emotional blunting in patients with depression.

## Methods/design

### Objective

The primary objective is to explore the efficacy and safety of fMRI-rTMS precise stimulation of right mPFC-amygdala individualized targets in the treatment of depression patients with emotional blunting.The secondary objective is to analyze the neuroimaging mechanism that may be related to depressive emotional blunting symptoms by comparing the differences in imaging changes before and after fMRI-rTMS treatment in combination with clinical efficacy and to verify the mechanism of mPFC-amygdala functional connection in depressive emotional blunting symptoms.

### Trial design

This trial is a randomized, controlled, double-blind, parallel-group, superiority, and single-center study in which eligible participants were randomly assigned to one of two groups: (1) fMRI-rTMS or (2) sham stimulation. Both groups received a combination of antidepressant medications. The study aims to compare the improvement of emotional blunting and depressive symptoms.

The Oxford Depression Questionnaire (ODQ) scores compared between the two groups at various time points served as the primary outcome measure [5]. Other depressive symptoms, such as the Montgomery and Asberg Rating Scale (MADRS) scale following the intervention, will be examined as the secondary outcome [17]. The evaluation time will be at the treatment baseline, after the 7th day of treatment, after the 15th day of treatment, and at the end of the 2nd, 4th, and 8th weekends after the treatment to further clarify the onset time and maintenance of fMRI-rTMS. In addition, structural and functional magnetic resonance imaging (MRI) is performed on the subjects using magnetic resonance imaging, combined with the precise targeted therapeutic effect of fMRI-rTMS on the functional connection of the mPFC-amygdala, to reverse verify the role of the mPFC and amygdala in the neural mechanism of depressive emotional blunting. This trial will follow the SPIRIT guidelines [18], and the SPIRIT checklist is shown in Additional file 1. The detailed flow chart is shown in Fig. 1. This study has been approved by the Ethical Committee of Xijing Hospital, Xian, China (XJLL-KY20222175) and is registered with the ClinicalTrials.gov database (NCT05555940).

**Fig. 1 Fig1:**
[figure not shown]
Flow chart of the trail design. *rTMS*, repetitive transcranial magnetic stimulation; *fMRI-rTMS*, functional magnetic resonance imaging-guided personalized rTMS

### Sample size

By reviewing the literature and using the primary outcome ODQ scores, the pre-set ODQ score of the fMRI-rTMS group was 63 ± 23 [19], while the ODQ score in the sham stimulation group was 80 ± 18 [20]. The significance level for the test was set at *α* = 0.05, the power at *β* = 0.1, with a confidence level of 0.9, and the sample size was determined to be 66 cases using PASS 11 software. Because of the potential loss of experimental data or subject withdrawal from the trial, the sample size was increased by 20%. To ensure the balance of the two groups, 80 cases were finally included in the trial.

### Participants and recruitment

This trial is expected to recruit 80 depression patients with emotional blunting aged between 18 and 65. All eligible participants attend the outpatient clinic at Xijing Hospital. Before enrolling all patients in the study, we will provide a comprehensive explanation of the study’s purpose, process, associated risks, and benefits. The patients will sign the informed consent form after they understand it. Patients participating in this study were completely voluntary and had the right to withdraw at any time. Professionally trained and experienced psychiatrists will screen patients who meet the inclusion criteria and undergo clinical assessment during follow-up. To recruit more patients, we placed a recruitment advertisement in the Xijing Hospital.

### Consent or assent: ancillary studies

This trial does not involve collecting biological specimens for storage.

#### Inclusion criteria

Outpatients of all genders, aged ≥ 18 years and ≤ 65 years, right-handed, admitted to the psychosomatic Department of Xijing Hospital;By the diagnostic criteria for depressive disorder of the Diagnostic and Statistical Manual of Mental Disorders, Fifth Edition (DSM-V);Montgomery and Asberg Depression Rating Scale (MADRS): total MADRS score ≥ 12;The total score of the ODQ at baseline was ≥ 50, and the answer to the standardized screening question of emotional blunting was “yes”: ‘*During the last week, to what extent have you been experiencing emotional side-effects of your antidepressant?’ The question’s subscript reads* ‘*Emotional side-effects are varied, but might include, for example — feeling emotionally ‘numbed’ or ‘blunted’ in some way/lacking positive emotions or negative emotions/feeling detached from the world around you/‘just not caring about things that you used to care about*’ [19].Received at least 6 weeks of monotherapy with an SSRI or SNRI before enrollment; andSubjects who can understand and are willing to strictly follow the clinical trial protocol to complete this study and sign informed consent.

#### Exclusion criteria

Having a history of substance abuse within 6 months before the start of the study;Patients with bipolar disorder and depression caused by other mental diseases (such as psychoactive substances and non-dependent substances);Having a history of severe somatic diseases or diseases that may affect the central nervous system (such as tumors and syphilis);Having neurological diseases or risk of seizures, such as previous brain diseases, head trauma, alcoholism, EEG abnormalities, MRI evidence of abnormal brain structure, or family history of epilepsy;There are contraindications to MRI scanning or transcranial magnetic stimulation treatment, such as metal or electronic instruments (intracranial metal foreign bodies, cochlear implants, cardiac pacemakers, stents, and other metal foreign bodies);Obvious suicide risk or actual suicide behavior within 6 months before the start of the study;Pregnant, breastfeeding, or planning pregnancy during the trial; andOther conditions that are not suitable for the study object in the researcher’s judgment.

#### Withdrawal or dropout criteria

The investigator has the right to terminate the participant's continued participation in this study if the following conditions are met:Subjects are found not to conform to the test protocol;Patients who do not wish to remain enrolled in the treatment;Request to change to another treatment;Inability to tolerate adverse effects; andDiagnosed with other psychiatric disorders after enrollment.

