### Follow-up

Researchers will check in with the patients by administering clinical scales and evaluating their cognitive function assessment at the end of the 2nd, 4th, and 8th weeks after treatment. The researcher will contact the patient in advance via telephone to remind them of the significance of the follow-up evaluation to ensure that the visit is not missed. Follow-up depends on the situation. Try to come to the hospital for follow-up after negotiation with the subjects, or use the self-assessment scale for telephone follow-up.

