### Statistical analysis

All data were analyzed based on the intention-to-treat principle, aiming to maintain the true state of the intervention as accurately as possible. Multiple imputations will be used to handle missing data.

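### The withdrawal rule lets the investigator end study participation, not only treatment, and nothing keeps ODQ collection going, so the intention-to-treat analysis may rest on imputed values for these patients

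*Protocol article*

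**What the plan says.** All references are to the protocol article.

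- **Withdrawal or dropout criteria.** The investigator has a right, not a duty, to end a participant's "continued participation in this study if the following conditions are met". The listed conditions are "Subjects are found not to conform to the test protocol", "Patients who do not wish to remain enrolled in the treatment", "Request to change to another treatment", "Inability to tolerate adverse effects", and a new psychiatric diagnosis after enrolment.
- **Statistical analysis.** "All data were analyzed based on the intention-to-treat principle", and "Multiple imputations will be used to handle missing data". The section names no missing-data assumption.
- **Follow-up.** Visits fall 2, 4 and 8 weeks after treatment, with reminder calls. Where a hospital visit is not possible, staff may "use the self-assessment scale for telephone follow-up". The section does not say whether this covers patients whose participation was ended.
- **Primary outcome measure.** The ODQ is self-rated.
- **Sample size.** ODQ means are 63 (SD 23) for active and 80 (SD 18) for sham. The total of 66 is raised by 20% for data loss or withdrawal, giving 80.

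**The concern.** The criteria treat two different events as one. A patient who no longer wants stimulation, or cannot tolerate it, has stopped treatment. That is not a refusal to fill in a questionnaire, and the right to withdraw from the study is granted separately under Participants and recruitment. Yet unwillingness to remain in treatment is listed as a ground for ending participation in the study.

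An intention-to-treat comparison is best served by observed outcomes for everyone randomised. If participation ends and assessment ends with it, the primary outcome goes missing because of events after randomisation that are plausibly tied to arm and response:

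- **Intolerance.** Harms lists headache, dizziness and scalp tingling as common reactions, and the sham section describes stimulation that induces no current. Intolerance could therefore be commoner in the active arm.
- **Change of treatment.** Patients who are not improving are the natural source of such requests.
- **Non-conformity.** The Intervention section requires the antidepressant to stay unchanged during the study. A patient who finishes all 15 sessions and later changes medication could meet this condition and lose the later assessments. Three of the five post-baseline time points come after stimulation has ended.

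Imputation under missing at random would then credit leavers with the course of comparable patients who stayed. If that is wrong by different amounts in the two arms, the primary contrast is biased.

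**Working it through.** **1. Plan's own figure and its allowance for loss.** Inputs from Sample size: difference 80 − 63 = 17; SDs 23 and 18; two-sided 5% (sidedness from Data analysis); power 90%.

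- Average SD = √((23² + 18²)/2) = √426.5 = 20.65.
- The normal approximation gives 32 per arm (64 in total). The t-based calculation with unequal variances gives power 0.899 at 32 per arm and 0.908 at 33, so 33 per arm are needed. The total of 66 is reproduced.
- 66 × 1.2 = 79.2, rounded up to 80.
- Room for patients without data, from every cause: 80 − 66 = 14, and 14/80 = 17.5%.

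**2. What happens to a patient whose participation is ended.** The withdrawal criteria end study participation. Follow-up does not extend its visits or telephone route to such patients. Statistical analysis imputes what is missing. Read together, these sections leave the later ODQ values to the imputation model.

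**3. Size of a possible bias.** Let p be the share of an arm that leaves, and δ the number of ODQ points by which the leavers' true mean is worse than the imputed mean. Then

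overstatement of the effect = p(active) × δ(active) − p(sham) × δ(sham).

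The article gives neither p nor δ for either arm, so the values below are assumptions.

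| Leavers, active arm | δ = 10, no sham offset | δ = 17 (no benefit at all), no sham offset |
|---|---|---|
| 10% | 0.10 × 10 = 1.0 | 0.10 × 17 = 1.7 |
| 20% | 0.20 × 10 = 2.0 | 0.20 × 17 = 3.4 |
| 30% | 0.30 × 10 = 3.0 | 0.30 × 17 = 5.1 |

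Against the planned 17 points, 1.7 is one tenth and 3.4 is one fifth.

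The sham term matters. If 20% also leave the sham arm and are imputed 5 points too favourably, the 3.4 becomes 3.4 − 0.20 × 5 = 2.4. If p × δ is equal in the two arms, the bias is zero.

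**4. Power.** Equal loss of 10%, 20% or 30% leaves 36, 32 or 28 per arm, with power 0.931, 0.899 or 0.856 for the planned difference. Up to about 20%, the issue is bias more than power.

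**The case against.** The strongest reply has four parts.

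- **Discretion and silence.** Ending participation is a right, and the article does not say that assessments then stop. It condenses a fuller protocol that is not shown and may cover this. A reader might infer that these patients' ODQ values are certain never to be collected; the text does not say so. This part stands as a limit on certainty. It does not remove the point, because the rule itself is in the article, is worded as leaving the study, and has no counterpart preserving follow-up.
- **Intention-to-treat is kept.** Imputation retains every randomised patient, so a reader who concludes that the plan contradicts the principle goes too far. The analysis is weakened where imputed values replace values that could have been observed. Details of the imputation model properly belong in an analysis plan, but no such plan can recover data that were not collected.
- **Some loss is unavoidable.** Two of the five conditions start with the patient, and patients may withdraw at any time. The reminder calls and telephone route show an effort to limit loss. This is fair, and it means that the full 17.5% allowance should not be attributed to this rule.
- **The illustration is one-sided.** It assumes no benefit in all active-arm leavers, imputation at the completer mean, and no offset from sham. Imputation can condition on baseline and day-7 ODQ, so a patient already seen not to respond need not be imputed as a responder. Non-responders may leave the sham arm just as often. All of this stands.

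A reader might also infer that the leavers are known to be those who do worst. The article gives no adverse-event rates by arm and no link between leaving and ODQ, so this is a plausible inference and not a documented fact.

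**Conclusion.** The point holds in a limited form. As worded, the criteria allow study participation to be ended for reasons plausibly related to arm and response, and no section keeps ODQ collection going. Where the right is used, the primary analysis would depend on an imputation assumption that the observed data cannot test.

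The number affected is unknown. The bias is 1.7 or 3.4 ODQ points at 10% or 20% loss from the active arm, but only if leavers have no benefit, are imputed like completers, and nothing offsets this in the sham arm. These are upper-end figures for those loss rates and should not be read as an expected bias. Conditioning on earlier ODQ scores and similar losses under sham would reduce them. A reader might take the 20% increase to mean an allowance of 16 of 80; the article's own figures leave room for 14. No view is taken on when treatment should be stopped.

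**What to change.** Amend the withdrawal criteria to separate discontinuation of study treatment from withdrawal from the study. Leave the clinical grounds for stopping treatment and the investigator's discretion unchanged; the amendment should not turn the listed conditions into mandatory stopping rules.

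State that a patient who meets a listed condition continues ODQ assessment, and the other scales where possible, at all remaining scheduled time points to week 8 unless consent is withdrawn. The telephone self-assessment route under Follow-up can be used where needed, since the ODQ is self-rated.

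Analyse all collected values in the arm as randomised, and impute only what is truly missing. A reference-based imputation, in which missing active-arm values are drawn from the sham-arm course, can be added as a sensitivity analysis.

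The cost is a protocol amendment, a few extra telephone assessments, and an effect estimate that may be slightly less favourable. Trial status describes recruitment as still open, so an early change protects the most data; values missed before it cannot be recovered by analysis.

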### Participant timeline

The time schedule of enrolment, interventions, assessments, and visits for participants is shown in Fig. 2.

**Fig. 2 Fig2:**
[figure not shown]
*rTMS*, repetitive transcranial magnetic stimulation; *fMRI-rTMS*, functional magnetic resonance imaging-guided personalized rTMS; *MRI*, magnetic resonance imaging; *ODQ*, Oxford Depression Questionnaire; *MADRS*, Montgomery-Asberg Depression Rating Scale; *HAMD-17*, Hamilton Depression Scale-17; *BSI-CV*, Beck Scale for Suicide Ideation-Chinese Version; *BDI*, Beck Depression Inventory; *SSRS*, Social Support Rating Scale; *LES*, Life Event Scale; *ISI*, Insomnia Severity Index; *THINK-it*, Cognitive function test; *PDQ-D*, Perceived Deficit Questionnaire for Depression; *CGI*, Clinical Global Impressions

## Methods: assignment of interventions

### Methods: assignment of interventions

Patients who meet the inclusion criteria will be randomly assigned to two groups: the fMRI-rTMS group and the control group at a 1:1 ratio. This study will utilize Excel software to generate random numbers using the function “ = RANDBETWEEN (1,500)”. The first number will be randomly determined, and then 80 numbers will be selected to match. The block randomization method will be used to assign participants to groups. The study population that meets the inclusion criteria, which includes depression patients with emotional blunting (*n* = 80), will be randomly divided into two groups, with 40 patients in each group.

### Concealment mechanism

To ensure the concealment of the assignment process, unblinded researchers will sequentially assign participants to groups and place the grouping information in an opaque, sealed envelope. Once the study has recruited participants and collected baseline information, the unblinded researcher will provide the envelope containing the group assignment results to the treatment administrator.

### Implementation

Upon receiving a sealed envelope from an unblinded person, the treatment operator will intervene with the participant according to the grouping specified in the envelope.

### Blinding

The specific allocation and treatment plan will be kept confidential from trial participants, outcome assessors, and data analysts. The researchers who met the entry criteria and conducted a follow-up clinical evaluation are professionally trained and experienced psychiatrists. Until the conclusion of the study, neither the participants nor the researchers were aware of the categorization. Unblinding is only done in the case of patient emergencies.

